**New fact**

Any new data that may lead to a reassessment of the benefit/risk ratio of the research or the product under investigation, to changes in the use of the product, in the conduct of the research, or in the documentation of the research, or to the suspension or discontinuation or modification of the protocol of the research or similar research. For trials involving the first administration or use of a health product in individuals who do not have a medical condition: any effect serious adverse event.

**Incident**

MDR, section 2 (64)

Any malfunction or alteration in the characteristics or performance of a device made available on the market, including an error in use due to ergonomic characteristics, as well as any defect in the information provided by the manufacturer and any undesirable side effect.

**Serious incident**

MDR, section 2 (65)

Any incident that directly or indirectly resulted or may have resulted or may have resulted in:

- a) death of a patient, user or any other person;
- b) a serious deterioration, temporary or permanent, in the state of health of a patient, user or any other person;
- c) a serious threat to public health.

**Investigation procedure**  
(preceding or concomitant with the SAE)

Notice to Sponsors from ANSM

the SAE)

All activities related to the use of the MD that are the subject of the study, imposed by the study protocol implemented before the occurrence of the adverse event or concomitantly and for which a causal relationship with this event is suspected. This notion includes, but is not limited to, additional invasive or cumbersome procedures in relation to the routine use of the device.  
For example: the surgical technique related to the placement of an implantable MD subject to a study, the use of imaging to monitor the placement of the MD studied.

**Serious threat to public health**

An event that may result in an imminent risk of death, serious deterioration of health or illness that may require prompt corrective action, and

|                                    |                                                                                                                                                                                                                                                                                                         |
|------------------------------------|---------------------------------------------------------------------------------------------------------------------------------------------------------------------------------------------------------------------------------------------------------------------------------------------------------|
| MDR article 2 (66)                 | likely to result in significant human morbidity or mortality or which is unusual or unexpected at the time and place of occurrence.                                                                                                                                                                     |
| Special situations          | Intentional, persistent or sporadic excessive use of drugs or products mentioned in article R. 5121-150 of the Public Health Code (CSP), accompanied by harmful physical or psychological reactions.                                                                                                    |
| - Abuse                            |                                                                                                                                                                                                                                                                                                         |
| -Medication error                  | Unintentional error by a healthcare professional, a patient or a third party, as the case may be, occurring during the care process involving a medicinal product or a healthcare product mentioned in article R. 5121-150 of the CSP, in particular during prescription, dispensing or administration. |
| - Misuse                           | Intentional and inappropriate use of a drug or product that is not in accordance with the marketing authorization or registration and good practice recommendations.                                                                                                                                    |
| - Overdose                         | Administration of an amount of drug or product, per dose or cumulatively, that is greater than the maximum dose recommended by the summary of product characteristics referred to in Article R. 5121-1, which is the subject of a clinical opinion.                                                     |
| User
MDR, section 2 (37) | Any health care professional or lay person who uses a device.                                                                                                                                                                                                                                           |

## 5.2. SPECIFICITIES OF THE PROTOCOL

### 5.2.1. Investigation procedure

The investigation procedure in this protocol corresponds to the placement, maintenance, daily change and removal of the attachment system (elastic adhesive band or cord + sheath) of the endotracheal tube.

### 5.2.2. Adverse events / Expected incidents

- List of Incidents/Expected Events related to the investigational medical device/comparator

- *The medical device under study (elastic adhesive tape):*

The MD is used in its indication: fixation.

(There is no detailed AE in the technical data sheet except for one contraindication: subjects sensitized to synthetic products).

Expected Incidents / AE:

- Intolerance to synthetic products
- Skin lesions and mucosal lesions in the path of fixation. (*13% of patients according to reference 7*)
- Loss of adhesiveness of the tape.

- *The medical device comparator (cord + sheath):*

The comparator is used in its indication: fixation.  
There are no AE detailed in the technical data sheet.

Expected Incidents / AE:

- Skin and mucosal lesions in the path of fixation (*43% of patients in reference 7*)
- Shearing, potential cut due to cord.

- List of expected AEs related to investigative procedures:

- *Medical device implementation:*

- Unscheduled extubations: self-extubations and accidental extubations during care (*7 to 16% of patients depending on reference 17*)
- Tracheal complications including laryngeal dyspnea
- Ventilator-associated pneumonia.

- List of expected AEs related to other additional procedures:

- *Auxiliary Drugs/MDs:*

- *Anti-adhesive (elastic adhesive tape group) to remove residual glue.*
- *Duoderm ® or other dressings used in curative treatment in case of lesions.*
- *Cavilon ™ type skin protection film.*

As these treatments are prescribed within the scope of their indications, any AEs for them are described in the respective summary of product characteristics (SPC)s, which serve as a reference.

-

*To the procedures performed, methods/techniques used for the purpose of the research:*

NA

- List of AEs related to the studied disease (death due to the disease, relapse, ...):

The patients included will be patients hospitalized in the intensive care unit, most often with multiple pathologies, who are intubated and put on invasive mechanical ventilation.

The potential complications of intensive care management of the study patients are identical to those expected in the non-study population, including, but not limited to, nosocomial infections, complications of intubation procedures, anesthesia drugs, consequences of prolonged bed rest, occurrence of shock with a risk of multi-visceral failure, and death.

These adverse events will be considered to be related to the disease being studied and not to the medical device being studied or to the investigative procedure.

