## **1.2.3. Benefit/risk balance**

The research manager qualifies the research as **interventional research with minimal risks and constraints**, since :

- ▮ All procedures are performed in a routine manner and defined in the decree of April 12, 2018 set by the ministry.

Indeed:

- The fastening systems proposed in the study are both systems most commonly used in France based on our survey conducted in January 2019 in 29 French ICUs. They are CE marked and will be used in accordance with their usual use in patients hospitalized in intensive care units.
- The change of fixation is performed daily by a qualified nurse in the ICUs in France.

The research does not focus on techniques or strategies that are neither innovative nor obsolete.

All patient management will be identical to usual practice. In particular, the date of discharge will be decided by the doctor in charge of the patient, independently of the study, but will be reported in the patient's file and the research CRF.

Consequently, the particular modalities of implementation in the research represent negligible constraints for the person who participate to the research. (Article R 1121-3 of the public health code (CSP), decree n° 2006-477 of 26 April 2006).

The sponsor will submit the study protocol to the Comité de Protection des Personnes Ouest IV-Nantes (Ethics Committee), before any implementation of the research, for a favorable opinion and confirmation of the qualification of the research, in accordance with article L 1121-1 of the Public Health Code (CSP) as they result from the laws n° 2004-806 of August 9, 2004 and n°2006-450 of April 18, 2006 relating to the public health policy.

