### **3. STUDY POPULATION**

#### **3.1. DESCRIPTION OF THE POPULATION**

The inclusion target is 768 patients in 16 investigating centers, i.e. 24 patients per center per inclusion period (see paragraph 6.2.1 Description of planned statistical methods).

Included patients will be patient admitted in ICU, requiring artificial ventilation with an orotracheal ETT for an estimated duration of more than 48 hours, as well as the use of vasopressors, and who will meet the inclusion and non-inclusion criteria described below.

Indeed, the fact that the patient is on vasopressors is an additional risk factor for pressure ulcers. The addition of this criterion makes the population more homogeneous. The results of this study could be extended to patients not on vasopressors.

In terms of potential recruitment, in the DEMETER project (study promoted by the CHD Vendée, NCT02515617), 10 of the 16 centers involved in FIXATUB study recruited 927 patients in 20 months (i.e. 741 in 16 months). The patients included in the DEMETER project met almost the same inclusion criteria as in FIXATUB. Thus, the recruitment of 3 intubated patients per month seems easily achievable in view of the population admitted to the ICU.

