### **3.3. CRITERIA FOR NON-INCLUSION**

- Pre-existing facial lesions on arrival in the intensive care unit on the path of the endotracheal tube fixation
- Admitted intubated following transfer from another intensive care unit
- Nasotracheal intubation
- Patient in isolation for suspected COVID or clinically proven COVID
- Patient admitted with tracheostomy
- Pregnant, nursing and parturient women
- Lack of social security affiliation
- Moribund (High probability of death within 48 hours of inclusion)
- Incapacitated adult (under guardianship, curatorship)
- Patient deprived of liberty by court order

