### **Inclusion**

This trial relates to care practice. In order to meet the main objective, it requires homogeneity of intubation fixation practices within a given department during each of both inclusion periods, regardless of the status of the patient in the study (included or not).

Thus, in each ICU participating in the project, whatever the inclusion arm considered (A or B), all patients requiring invasive mechanical ventilation (MV) from their admission to the intensive care unit (if the respiratory assistance was set up before admission to the intensive care unit) or from the moment the respiratory assistance was set up (if it was set up in the intensive care unit), will benefit from the fixation method according to the inclusion arm (A or B) described above, whether they are included in the study or not. D0 is defined as the first day of the study fixation system of the ETT (cord + sheath or elastic adhesive bands).

Information and consent to participate in the study will be sought from patients requiring MV (or their relatives), who meet all the inclusion criteria and have no non-inclusion criteria (see chapter 3.3).

In the absence of the physical presence of the trusted support person or a relative, an emergency procedure will be available to include the patient. In all cases, the relative and then the patient will be informed as soon as possible by the investigator who will deliver the information note and the collection of their oral consent will be carried out secondarily by the investigator.

After having ensured the consent of the patient or his relatives or having followed the emergency inclusion procedure, the investigator can then include the patient before the D1 photograph. Moreover, if the information was initially given to the relatives, the consent will also be sought from the patient as soon as his level of vigilance allows it.

One of the criteria for non-inclusion of the patient is the presence of pre-existing facial lesions on arrival in the ICU in the path of the endotracheal tube fixation.

When the patient is admitted to the ICU already intubated, the tube is already fixed and this fixation is generally changed in order to put in place the fixation system used in the department. Within the framework of the protocol, we will ask that it be systematically changed to install the fixation system under study. The non-inclusion criterion can therefore be assessed at this point.

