#### **4.4. DESCRIPTION AND JUSTIFICATION OF THE INTERVENTION STUDIED**

The FIXATUB study is a cluster and crossover randomization study. Patients will be included over 2 periods of 12 months. The timing of both periods (period with the use of the elastic adhesive tape and period with the use of the cord associated with a protective sheath) will be randomly assigned for each center. The sponsor will provide the fixation systems for each period.

There are 3 cord + sheath type fastening systems currently available:

Teleflex® ETT fixation straps, Int'air® medical straps and CairLGL® fixation laces. All 3 are made of cotton tape and a flexible PVC protective sheath and are all 3 classified as MD class 1 non-sterile. No data is available to evaluate the superiority of one of these sheaths.

Each center provided us with their annual consumption of ETT fixation systems in order to obtain a precise evaluation of the quantity of devices required for the project. The quantity of sheaths required being important and the sheath being more expensive than the adhesive elastic band, we will proceed to an "adapted" tender procedure for these 3 suppliers and the devices being similar, the least expensive offer will be chosen.

As for the elastic adhesive tape, we will carry out a competition between the various suppliers and will opt for the least expensive.

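### The tape's one recorded contraindication is neither a non-inclusion criterion nor an exemption from the centre-wide fixation rule: a minor patient-safety gap

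*Protocol*

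**What the plan says.** Section 5.2.2, in its list of expected incidents for the elastic adhesive tape, notes from the technical data sheet "one contraindication: subjects sensitized to synthetic products". It then lists "Intolerance to synthetic products" among the incidents to expect with the tape.

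Section 3.3 has ten non-inclusion criteria. The only one about the skin of the face is "Pre-existing facial lesions on arrival in the intensive care unit on the path of the endotracheal tube fixation". None concerns allergy, sensitisation or a contraindication to either device, and the inclusion criteria in section 3.2 add nothing on this.

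The Inclusion part of section 4.3 assigns the unit's current fixation to "all patients requiring invasive mechanical ventilation (MV) from their admission to the intensive care unit" or from the start of ventilation in the unit, "whether they are included in the study or not". Patients who arrive already intubated have their fixation replaced as a matter of course by the study system. No exception is stated. Section 4.1 adds that the previous system leaves the department's stock at the end of a period.

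On the other side, section 1.2.3 says that the two CE-marked systems "will be used in accordance with their usual use in patients hospitalized in intensive care units", and section 5.2.2 says that the tape is used within its indication, which is fixation.

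**The concern.** The protocol records a reason not to use one of its two devices, then fixes an allocation rule that takes no account of it. A nurse who learns of a known sensitisation during a tape period finds nothing in sections 3.3 or 4.3 that excludes the patient or permits another fixation.

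What is at stake is patient safety on a small scale. The safeguards that the protocol does contain act after exposure: intolerance is an expected incident (5.2.2), lesions are checked daily (4.3, Follow-up), and misuse is a special situation to be notified (5.1 and 5.3.4). Section 5.3 also keeps fixation-related peri-oral lesions out of the adverse event table, so a reaction to the tape around the mouth might be recorded only as a lesion. None of this stops the tape being placed on a patient already known to be sensitised.

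**Working it through.** **Setting the sections side by side**

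1. Section 5.2.2: sensitisation to synthetic products contraindicates the tape.
2. Section 3.3: a sensitised patient with intact facial skin meets none of the ten non-inclusion criteria.
3. Section 4.3: the patient receives the unit's allocated fixation, and a patient who declines the study or is otherwise not included receives it too. A new non-inclusion criterion alone would therefore not protect everyone; the rule itself needs an exemption.
4. Section 4.7.1: the listed reasons for ending participation early are withdrawal of consent and transfer to another intensive care unit. Intolerance is not among them.
5. Sections 1.2.3 and 5.2.2: conforming use is stated in general terms, with no screening step, exclusion or exemption.

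**Size of the problem**

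The documents give no prevalence of known sensitisation. For illustration only, assumed rates of 0.5% to 5% among the 384 included tape-period patients (768/2) give about 2 to 19 patients (384 × 0.005 = 1.9; 384 × 0.05 = 19.2). Non-included patients under the centre-wide rule would be additional and cannot be counted.

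**Cost of excluding such patients**

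Inputs from section 6.2.2: 35% against 20%, 16 centres, m = 24 per centre-period, intra-class correlation 0.10, inter-class correlation 0.05, alpha 5% (taken as two-sided).

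- Design effect: DE = 1 + (m − 1) × 0.10 − m × 0.05.
- Effective number per arm: n = 16m/DE.
- Power: Φ(0.15/√(0.3875/n) − 1.96), where 0.3875 = 0.35 × 0.65 + 0.20 × 0.80.

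The plan's own figure first. At m = 24, DE = 1 + 2.30 − 1.20 = 2.100 and n = 384/2.100 = 182.9, so power is 90.29% (89.80% with the pooled variance under the null). The stated 90% is reproduced.

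No replacement, at assumed exclusion rates x:

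| x | Excluded of 768 | m | DE | n per arm | Power | Power, pooled variance |
|---|---|---|---|---|---|---|
| 1% | 7.7 | 23.76 | 2.088 | 182.1 | 90.17% | 89.67% |
| 2% | 15.4 | 23.52 | 2.076 | 181.3 | 90.05% | 89.55% |
| 5% | 38.4 | 22.80 | 2.040 | 178.8 | 89.66% | 89.14% |

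The loss at 5% is 90.29 − 89.66 = 0.63 points.

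With replacement, each centre needs 24/(1 − x) otherwise eligible patients per 12-month period: 24.24, 24.49 or 25.26, which is 2.02, 2.04 or 2.11 per month against 24/12 = 2.00 now. Section 3.1 says "the recruitment of 3 intubated patients per month seems easily achievable". I read this as per centre; the recruitment it cites, 927 patients in 10 centres over 20 months, is 927/(10 × 20) = 4.6 per centre per month. Replacement is feasible.

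**The case against.** The strongest reply is that the centre-wide rule was never meant to be exhaustive. Taken word for word it would also cover nasotracheal and tracheostomy patients, to whom a fixation for an oral tube cannot apply. Its stated purpose is uniform practice within a unit, not suspension of ordinary contraindications. The wording on usual use and indication, and the treatment of misuse as notifiable, show that the data sheet is expected to be respected. A sensitised patient given another fixation would be a recorded deviation, reviewed under section 6.2.7. The source sentence is also thin: a parenthesis about a tape whose supplier section 4.4 leaves to price competition.

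Much of this stands. A reader might infer that the protocol orders staff to override the data sheet. It does not, and its general wording leans the other way. But that wording neither excludes the patient nor exempts the patient from the rule, and recording a deviation afterwards is not provision for it. The open choice of supplier is a reason to word the criterion by data sheet, not to omit it.

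Two objections to the remedy also stand. The trial is open and inclusion is allowed up to the D1 photograph, so a history of sensitisation might be sought harder in tape periods. And any substitute brings back, on a small scale, the coexistence of systems that section 4.1 wants to avoid.

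**Conclusion.** The point holds as a minor patient-safety improvement. The protocol records a contraindication, does not act on it in the eligibility criteria, and states an allocation rule whose literal reading conflicts with it. The sections can be compared directly, so confidence in the omission is high. How many patients it touches cannot be derived, and only known cases could be caught, because section 4.3 notes that patients are often unconscious.

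A reader might also infer that the comparison of lesion rates is compromised. The documents do not support that: they give no rate of sensitisation, and nothing suggests a number large enough to move a contrast of 35% against 20%. The 1% to 5% exclusion rates are assumptions that price the remedy; they do not measure harm.

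**What to change.** - **Section 3.3:** add *known sensitisation or other contraindication listed on the data sheet of either study device*. Check it from records or relatives with the same question at D0, in both arms and both periods, and enter it by arm in the screening log that section 4.3 already requires.
- **Section 4.3, Inclusion:** add *except where contraindicated by the device data sheet* to the centre-wide rule, for included and non-included patients alike. Leave the substitute fixation to the clinician. It should not be assumed to be the study cord, because section 4.4 says of the three candidate cord systems: "All 3 are made of cotton tape and a flexible PVC protective sheath". The sheath is itself synthetic.

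The cost is one criterion, one clause and a log entry, and it has three downsides:

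- A few patients are excluded, replaceable at the recruitment rate in section 3.1.
- There is a small risk of uneven ascertainment between arms, which can be checked by comparing the logged exclusions.
- A non-study fixation is occasionally used in a unit.

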### **5.2.3. Events of interest**

Within the framework of the evaluation of both MD (cord + sheath and adhesive elastic band) the **events of interest** induced by these MDs will be collected.

These are:

- Self-extubations
- Laryngotracheal dyspnea
- Ventilator-associated pneumonia

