#### 5.4.2. Declaration to the Competent Authority

The sponsor must report to the Competent Authority "**reportable events**"; **any serious adverse event** with a proven or reasonably foreseeable causal link (possible, probable, certain) with the investigation procedure, the new facts and, if applicable, the measures taken, as from the day on which it becomes aware of them. Only causality level 1 (i.e. "unrelated") is excluded from reporting. Deadlines for reporting by the sponsor to the ANSM :

| Type of event                                                                                                                                                                     | Time limit for initial declaration / Follow up                          |
|-----------------------------------------------------------------------------------------------------------------------------------------------------------------------------------|-------------------------------------------------------------------------|
| New fact                                                                                                                                                                          | WITHOUT DELAY                                                    |
| A "reportable" event (SAE) that has resulted in death, imminent risk of death, serious injury or illness and requires prompt corrective action or new information on these cases. | WITHOUT DELAY and at the latest within 2 calendar days* . |

|                                                                                                                                                                                          |                                                                         |
|------------------------------------------------------------------------------------------------------------------------------------------------------------------------------------------|-------------------------------------------------------------------------|
| This includes relevant and unexpected events when they become a potential public health hazard. It also includes the possibility of multiple deaths occurring at short intervals. |                                                                         |

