### **Role:**

- Monitor the progress of the study, the characteristics of the patients included and the frequency of events of particular interest (self-extubations and repositioning of the endotracheal tube).
- Provide an advisory opinion on whether the trial should continue.
- The CIS is also notified of all security information transmitted to the appropriate authorities.

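### The disease-attribution rule closing protocol section 5.2.2 contradicts the listing of ventilator-associated pneumonia as procedure-related, so a serious case can miss SAE notification and authority declaration

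*Protocol*

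**What the plan says.** Protocol section 5.2.2 sets out several headed lists. Under "List of expected AEs related to investigative procedures" it names unscheduled extubations, "Tracheal complications including laryngeal dyspnea" and "Ventilator-associated pneumonia". Section 5.2.3 says that the events of interest "induced by these MDs will be collected"; they are self-extubation, laryngotracheal dyspnoea and ventilator-associated pneumonia.

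The last list in 5.2.2 concerns the underlying disease. It is open-ended and covers "nosocomial infections, complications of intubation procedures, anesthesia drugs, consequences of prolonged bed rest", shock with organ failure, and death. The section then closes with the rule that these events "will be considered to be related to the disease being studied and not to the medical device being studied or to the investigative procedure".

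Section 5.3 asks the investigator for an independent judgement of intensity, causality and seriousness for every adverse event entered in the e-CRF. Section 5.3.2 gives the criteria and makes *possible* the category to use when the link cannot be assessed. Section 5.4.2 states that only the unrelated category "is excluded from reporting" to the authority.

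**The concern.** Ventilator-associated pneumonia is a hospital-acquired infection. The protocol therefore gives two answers about the same event: it is expected from the study procedure and brought about by the devices, and it is also declared in advance to be due to the disease and to neither of these. Nothing says which statement prevails.

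This matters because causality decides the reporting route. A centre that follows the procedure list and a centre that follows the closing rule could handle the same serious pneumonia in opposite ways, and the second would withhold it from the two steps that depend on a suspected link.

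**Working it through.** No figure in the protocol bears on this point, so the check sets the provisions side by side and follows one event through them.

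**1. Does one event fall under both rules?**

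| Event | Procedure list, 5.2.2 | Event of interest, 5.2.3 | Disease list and closing rule, 5.2.2 |
|---|---|---|---|
| Ventilator-associated pneumonia | named | named | covered, as a hospital-acquired infection |
| Laryngeal dyspnoea | named | named | not named; covered only if read as a complication of intubation |
| Other tracheal complications | named as a class | not listed | same, by interpretation only |
| Self-extubation | named | named | not named |
| Accidental extubation during care | named | not listed | not named |

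The overlap is direct for pneumonia and arguable for laryngeal and tracheal complications. For extubation events the disease list has no matching entry.

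**2. Does the rule fit the causality section?** Section 5.3 asks for a judgement on each recorded event, and 5.3.2 sends doubtful cases to *possible*. The closing rule fixes the answer as not related before any judgement is made. Both cannot be followed for the same pneumonia.

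**3. What follows for a serious pneumonia?** Take one that prolongs the hospital stay or ends in death, and so meets the definition of an SAE in 5.1.

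- *Following the procedure list and 5.3.2:* it is at least possibly related. Under 5.3.3 and 5.3.4 it is entered in the e-CRF and the SAE form goes to the sponsor within 3 calendar days, with detailed follow-up. Under 5.4.2 it is declared to the authority within 2 or 7 calendar days, depending on its type.
- *Following the closing rule:* it is not related. Under 5.3.4 it is still entered in the e-CRF as an event of interest within 3 calendar days, because that route carries no causality condition. The SAE form is not triggered, since 5.3.3 and 5.3.4 require it only for serious events suspected to be linked to the procedure. Declaration is not triggered either, since 5.4.2 leaves out the unrelated category.

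The two readings differ in the SAE form, its follow-up and the declaration. They do not differ in whether the event is recorded.

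**4. Is there an unconditional route for every event in the overlap?** There is for pneumonia and laryngotracheal dyspnoea. Tracheal complications other than dyspnoea are not events of interest, so if the closing rule were applied to them, nothing in 5.3.4 would bring them to the sponsor as events of interest.

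**The case against.** The strongest defence is that the sections can be read together. The closing rule ends a list of background intensive-care complications, whereas pneumonia on the ventilator is named specifically elsewhere, twice. A careful site would let the specific entry prevail over the general one. Section 5.3 would still require a causality judgement, 5.3.2 would supply *possible* as the default, and a case judged so would go to the SAE form and the authority. Section 5.4.1 also has the sponsor assess the causality of SAEs and monitor device-related complications through the event table.

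Much of this stands and limits the point. A reader might infer that the rule switches off causality assessment, or that these events escape the record. The documents support neither: the individual assessment in 5.3 remains in force, and events of interest are entered within 3 calendar days regardless of cause.

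A reader might also take laryngeal dyspnoea to be as plainly contradicted as pneumonia. It is not. Section 5.2.1 defines the investigation procedure as handling the fixation system, not the act of intubating, so complications of intubation may be meant as something separate.

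What does not stand is that these safeguards settle the pneumonia conflict. Giving priority to the specific entry is a sensible convention, but the protocol does not state it, and the closing rule is worded as an instruction without exception. The sponsor's causality review concerns SAEs, and nothing in the text tells the sponsor's assessor to depart from the protocol's own rule.

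**Conclusion.** The protocol is wrong as written on a narrow point. Ventilator-associated pneumonia is procedure-related and device-induced under two lists and unrelated to both under a rule that admits no exception. That rule also conflicts with the individual assessment and the *possible* default. Laryngeal and tracheal complications are affected only if they are read as complications of intubation.

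Followed literally, the rule would keep a serious pneumonia out of SAE notification, the associated follow-up and the declaration to the authority. This assumes that a centre applies the closing rule in preference to the procedure list, which the text permits but does not compel. Recording in the e-CRF is unaffected. The primary and secondary endpoints in section 2 do not include pneumonia, so the comparison of the two fixation systems on those endpoints does not depend on this point.

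The size in cases cannot be given, because the protocol states no rate for pneumonia or dyspnoea. A reader might reach for the 7 to 16% in section 5.2.2, but that range is for unscheduled extubation, which the disease list does not name. A reader might also see an error in the shorter list of events that section 5.6 gives the safety committee. A committee list may differ from 5.2.3 in purpose, the committee is also told of safety information sent to the authorities, and the documents do not show the difference to be a mistake.

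**What to change.** Reconcile sections 5.2.2 and 5.2.3 with 5.3 and 5.3.2 by adding one sentence after the closing rule of 5.2.2. It should say that the rule does not apply to events listed in 5.2.2 as related to the investigation procedure or in 5.2.3 as events of interest, and that the causality of these events is assessed case by case under 5.3.2, including its default.

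The cost is a change of wording in the safety section, a note to the centres and possibly some additional SAE forms; their number cannot be estimated from the protocol. No endpoint, sample size or analysis changes.
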